#### Implementing the Intervention

In this stage, the PLUMS intervention will be delivered over an 8-week period at the household level in the intervention arm, as already described (Supplementary Table 2 in Multimedia Appendix 5). The objectives of the intervention are to reduce the ST of children [18], enable the caregivers with positive parenting skills and ST literacy, and propose unplugged family time in the home environment.

Participants in the intervention arm will also be classified into 5 behavior stages of change as per the transtheoretical model [45]. In the control arm, routine home-based and facility-based health services will be continued by the local auxiliary nurse midwife under the public health system. Compliance of the intervention will be checked via a proforma from parents (Supplementary Table 3 in Multimedia Appendix 5) and via a journal, videos, or pictures maintained by families.

#### Postintervention Assessment

In this stage, the same questionnaire for ST and its correlates as used in the baseline assessment will be administered to the intervention and control groups immediately and 6 months postintervention. Hence, primary and secondary outcome measures will be assessed at these 2 time points. In addition to the 2 months of active intervention, the researcher will maintain contact with the intervention arm group participants during the 6-month follow-up period. A passive intervention via information education material (text messages, telephone, emails, or mail) to parents will be given during the follow-up period.

This intervention study will take place over a period of 8 months. The baseline data collection will take place before the intervention (t_0_). The postintervention phase (t_1_) and follow-up assessment will be done at 6 months (t_2_), as shown in Supplementary Table 4 in Multimedia Appendix 5, as per the Standard Protocol Items: Recommendations for Interventional Trials (SPIRIT) [46].

#### Outcomes

The primary outcome (caregiver-reported) measure will be the mean change in ST (in minutes) per day separately for weekdays and weekends. The secondary outcomes (caregiver-reported) will be the mean change in the duration of physical activity (in minutes), proportion of children with emotional behavior problems, and sleep disturbances. For emotional behavior and sleep disturbances, the change in scores as per the tools will be noted, as mentioned earlier.

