**Methods:**

A theory-based multicomponent intervention known as Program to Lower Unwanted Media Screens (PLUMS) at the household level has been developed. It is based on the social cognitive theory for children and self-determination theory for caregivers. After pretesting, a randomized control trial will be conducted to assess this intervention's effectiveness among healthy children aged 2-5 (±3 months) years and their primary caregivers who have at least one digital media gadget at home in zone three of Chandigarh (population of 2,730,035). A sample size of 428 children is estimated per arm. PLUMS includes disseminating specific information, education, communication in the form of videos and posters to the primary caregivers, and conducting motivational interviewing as and when needed. Children will be provided suggestions for playful activities as alternatives to digital media gadgets. The primary outcome is the mean change in the duration of screen time, and secondary outcomes are sleep duration and patterns, emotional-behavioral problems, and level of physical activity of the children. Per-protocol and intention-to-treat analyses will be conducted using SPSS for Macintosh, Version 25.0.

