#### Sample Size

The sample size for the individual level randomization was estimated using the following formula [38]: n_I_= (σ_1_^2^+σ_2_^2^) (Z_1-α/2_+ Z_1-β_)^2^/Δ^2^, where n = sample size, σ_1_ = standard deviation of the control group and assumed to be 2.09 [39], σ_2_ = standard deviation of the intervention group and assumed to be 1.46 [40], Δ = difference in group means of the average ST and assumed to be 0.54 [39], Z_1-α/2_ = two-sided Z value (Z = 1.96 for the 95% CI), and Z_1-β_ = power (80%). Hence, n_I_ was 170 participants per arm. Considering a 10% attrition rate due to loss to follow-up and 15% nonresponse or refusal rate, the sample size per arm was calculated as 214.

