#### Data Management and Analysis

Quantitative data from the intervention study will be entered into Microsoft Excel and analyzed using SPSS for Macintosh, Version 25.0 (IBM Corp, Armonk, NY). ST on a weekday and weekend day will be calculated separately as per available literature [47]. So, the average ST (by viewing any type of media gadget) per day in a week will be calculated, and because there are 5 weekdays (Monday to Friday) and 2 weekend days (Saturday and Sunday) in a week, the weighted average ST per day in a week will be calculated as: Average ST per day (minutes) = [(Weekday ST in minutes x 5) + (Weekend ST in minutes x 2)]/7.

Continuous variables will be summarized as means with interquartile ranges and standard deviations. Correlations between a continuous variable and other variables will be estimated. Categorical variables will be summarized as proportions, and differences between groups will be tested using chi square tests. The data will be analyzed as per intention-to-treat analysis (for their initially assigned study arm) and per-protocol analysis. Relative risks and their effect sizes, together with the corresponding 95% CIs, will be estimated. The effectiveness of the intervention will be estimated by calculating the relative risk reduction (1-relative risk). A *P* value <.05 will be considered statistically significant for all analyses.

Information regarding PLUMS will be shared in the first communication and then reinforced every week for 8 weeks. So, participants who withdraw from the trial after the third week will be included in the analysis. Participants who withdraw any time before the third week will be excluded from the analysis.

Caregivers’ knowledge will be analyzed at the end of the intervention if no associations are observed. The proforma on behavior change will be completed at baseline (t_0_) and endline (t_1_) to determine the stage of change the families are at postintervention.

A feedback/compliance questionnaire (Supplementary Table 3 in Multimedia Appendix 5) will be given to the caregivers at each counseling session (weekly) to check their fidelity. The child's fidelity, including the level of engagement, will be checked with personalized journals comprising the activities they performed during the given intervention. The parents will be contacted via their preferred mode of communication weekly to keep them motivated and disseminate the next week's intervention module.

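### Outcomes makes weekday and weekend screen time separate primary measures, but the trial is sized on one comparison of average screen time and no decision time point is named

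*Protocol article*

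**What the plan says.** The relevant statements are spread over several sections of the protocol article.

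- **Outcomes:** "The primary outcome (caregiver-reported) measure will be the mean change in ST (in minutes) per day separately for weekdays and weekends".
- **Abstract, Methods:** "The primary outcome is the mean change in the duration of screen time". There is no weekday/weekend split and no time point.
- **Sample Size:** one two-sided comparison with Z = 1.96 and 80% power, based on the "difference in group means of the average ST and assumed to be 0.54".
- **Data Management and Analysis:** weekday and weekend ST are each calculated, and then "the weighted average ST per day in a week will be calculated as" five times the weekday value plus twice the weekend value, divided by seven.
- **Postintervention Assessment:** measurement takes place immediately and 6 months after the intervention, and "primary and secondary outcome measures will be assessed at these 2 time points". Neither is ranked above the other.
- **Data Management and Analysis:** both intention-to-treat and per-protocol analyses are planned, and a P "value <.05 will be considered statistically significant for all analyses".

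**The concern.** The quantity that the trial is powered for (average ST, compared once at 5%) is not what Outcomes declares primary (weekday change and weekend change, separately). The weighted average that would link the two is defined, but Outcomes does not give it primary status. Two unranked time points and one significance threshold for everything leave several candidate headline results.

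Two things are at stake. If a significant result on any candidate could support a claim of effectiveness, the 5% error rate behind the sample size would not hold. The deciding comparison could also be settled after the data are seen. This matters more than usual here. The Randomization section says that the same person generates the sequence, collects the data and delivers the intervention. Blinding is limited to data entry, and the outcomes are caregiver-reported.

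**Working it through.** **1. Reproduce the plan's sample size.** Inputs from Sample Size: SDs 2.09 (control) and 1.46 (intervention), difference 0.54 (unit not stated; hours assumed), two-sided 5%, power 80%.

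n per arm = (2.09² + 1.46²)(1.960 + 0.8416)² / 0.54² = (4.3681 + 2.1316) × 7.849 / 0.2916 = 174.95, so 175. The stated 170 is within 3% of this. The formula uses an undivided 5% for a single comparison, so the stated size fits one primary comparison.

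**2. Count the candidate primary comparisons.** Two measures (weekday, weekend) × two time points (immediate, 6 months) = 4. Per-protocol repeats are not counted.

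**3. Family-wise error if any one of the four sufficed.** Under independence: 1 − 0.95⁴ = 18.5%. For jointly normal test statistics this is the upper bound. The four results come from the same caregivers reporting on the same children, so positive correlation is expected. The documents give no correlations, so these are assumptions. Simulation of four two-sided tests at 5% (1,000,000 draws) gave:

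| Assumed correlation | All pairs equal | Product structure (measure × time) |
|---|---|---|
| 0.5 | 15.6% | 16.1% |
| 0.7 | 13.1% | 13.7% |
| 0.9 | 9.4% | 9.8% |

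These rates count false positives in either direction. With the correlations shown, a false claim of benefit is about half as frequent: roughly 7.8%, 6.5% and 4.7% in the equal-correlation case, against a nominal 2.5%.

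**4. What each resolution would need**, from the formula in step 1 with alpha changed:

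| Primary family | Alpha per test | Evaluable per arm for 80% power | Power at 170 per arm |
|---|---|---|---|
| One comparison | 0.05 | 175 | 78.9% |
| Two (Bonferroni) | 0.025 | 212 | 69.9% |
| Four (Bonferroni) | 0.0125 | 249 | 60.4% |

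The Results section reports 440 enrolled. If they are split 1:1 (220 per arm) with the assumed 10% attrition, 220 × 0.90 = 198 per arm remain. Power is then 84.6% for one comparison at 5% and 68.5% for each of four at 1.25%. The two- and four-comparison figures assume that the stated difference and SDs apply equally to weekday and weekend ST. The documents give no separate values, and no SD for change.

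**The case against.** The strongest reply is that the article already points to one quantity. Data Management and Analysis can be read as computing weekday and weekend ST only as components of the weighted average. The Abstract, the Study Objectives, the Sample Size section and the Discussion's Principal Findings all speak of a single mean or average, and even Outcomes uses the singular. This stands in part. A reader might infer that the trial has no identifiable primary quantity at all, and the documents do not support that. But the wording in Outcomes still contradicts this reading, and Outcomes is where a reader looks for the definition.

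A second reply is that the four tests are inferred. The article says that outcomes are assessed at two time points. It does not say that each measure is formally tested at each, and it states no rule that one significant result is enough. This also stands, so the error rates above are conditional. A reader might quote 18.5% as the trial's error rate, but that needs independence, which is implausible here. A reader might also count per-protocol results to reach eight primary tests. Reporting both analysis sets is routine, the two are highly correlated, and nothing makes per-protocol a separate route to success.

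Third, Study Objectives does give a criterion for effectiveness, a percentage risk reduction of mean ST, so it would be wrong to say that none exists. It is poorly specified, because a mean has no risk, and it names neither the form of ST nor the time point. It does not settle the matter.

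Finally, multiplicity handling may be left to an analysis plan that is not shown. Silence on that would be no finding. The conflict between Outcomes and Sample Size is stated in the article itself, and a later document can resolve it only by overriding one of the two.

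**Conclusion.** The point holds as an inconsistency to be reconciled. Outcomes splits the primary measure by weekday and weekend, while the sample size rests on one comparison of average ST and the analysis section builds a weighted average without primary status. Confidence in that conflict is high.

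Its size is conditional. If any one of up to four unadjusted comparisons were enough, the two-sided error would be about 9% to 16% instead of 5%. This rests on assumed correlations of 0.9 to 0.5 and on a success rule that the article does not state. The documents favor neither time point as the decisive one, so the supported conclusion is that one must be named, not which.

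**What to change.** Reword Outcomes so that it agrees with Sample Size and Data Management and Analysis. State one primary: the between-arm difference in change in 5:2 weighted average ST per day, by intention to treat, two-sided 5%, at one time point (t1 or t2) that the sponsor specifies before outcome analysis. List weekday ST, weekend ST, the other time point and the per-protocol results as secondary or supportive.

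The cost is wording, plus the loss of primary status for the split results, which are still reported. The sample size is unchanged: the plan's formula needs 175 evaluable per arm, and 198 would remain from the 440 enrolled under a 1:1 split and 10% attrition. Keeping all four comparisons as primary with Bonferroni control would instead need 249 evaluable per arm, more than the 220 per arm enrolled under that split.

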#### Randomization

Computer-generated randomization will be done to select families for the intervention and control arms. However, restricted randomization will be done so that intervention and control groups have a similar number of families from high, middle, and low socioeconomic groups. Geographical differences (urban and slum areas) in the study area will also be considered during randomization to avoid contamination. A computer-generated sequence will be used to allocate the families in the intervention and control groups. The person generating the list of sequences, collecting data, and disseminating the intervention will be the same; hence, concealment might not be possible. Moreover, as the intervention package comprises information, education, and communication material, concealment might not be possible. Data collection and delivery of the intervention will be done only after the family’s allocation in the intervention or control arm.

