#### Baseline Assessment

The baseline data were collected from December 2019 to March 2020. During the baseline assessment, the mean ST, prevalence of excessive ST and its correlates, mean duration of physical activity, emotional problems, and sleep disturbances in both the intervention and control arms were measured.

To assess mean ST, physical activity, and prevalence of excessive ST, a pretested, validated, semistructured, bilingual (English and Hindi languages) digital screen exposure questionnaire (DSEQ) was used (Multimedia Appendix 7). The DSEQ was developed in 5 phases. In phase 1, a draft questionnaire was developed by reviewing the literature on existing tools (n=2) from 2009 to 2017. In phase 2, 9 experts assessed the draft Hindi and English questionnaires’ face and content validity. Face-to-face interviews with primary caregivers (n=30) were conducted in a tertiary care hospital for acculturation. In phase 3, a pilot study was conducted among randomly selected families to evaluate the feasibility of the DSEQ in field settings. During phase 4, test-retest reliability was assessed among 30 primary caregivers selected randomly in another urban cluster. In phase 5, the internal consistency of the DSEQ was checked by conducting a cross-sectional study among 400 randomly selected, primary caregivers in Chandigarh, North India. The DSEQ has good internal consistency (Cronbach α=0.73-0.82) and inter-rater agreement (kappa 0.75, 95% CI 0.72-0.78).

The DSEQ was used to collect information from the primary caregivers of the children on (1) sociodemographic profile including family type and socioeconomic status (BG Prasad classification, 2016) [42], (2) digital screen exposure and home media environment, (3) level of physical activity of the child, (4) child’s media-related behaviors, and (5) parental perceptions and literacy regarding digital screen exposure. We recorded the duration and content of media watched by the child on a typical day. The objective criterion to measure ST was the number of hours the child watched a specific TV program. Cinema and movies were excluded from the ST measurement to calculate the actual average of ST for a regular day. Besides, cinema and movies are not watched daily and might falsely increase ST.

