## Results

Enrollment of all participants (n=440) was completed during the baseline assessment. The intervention phase could not be started due to restrictions imposed under lockdown to contain the Covid-19 pandemic. Considering the Covid-19 pandemic and likely change in the ST and physical activity of the children, we will measure the ST and physical activity again before delivering the intervention. The intervention was started in November 2020. It will be implemented for 8 weeks. The endline assessment will be done immediately postintervention and after the 6 months of follow-up. The results will most likely be published by 2022.

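### The primary outcome is a change in screen time, but the trial is sized on group SDs, two baselines are possible, and no listed analysis uses baseline or the randomisation factors; naming a baseline-adjusted model would be a free gain

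*Protocol article*

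**What the plan says.** The Outcomes section of the protocol article sets the primary outcome as "mean change in ST (in minutes) per day", with weekdays and weekends taken apart.

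The Sample Size section uses the two-means formula with a "standard deviation of the control group and assumed to be 2.09" and a "standard deviation of the intervention group and assumed to be 1.46". The difference is 0.54 in mean screen time, two-sided at 5%, with 80% power. The results are 170 per arm before inflation and 214 after. It gives no SD of change and no correlation between baseline and follow-up.

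On baseline, the Baseline Assessment section says: "The baseline data were collected from December 2019 to March 2020". The Results section says that the intervention was held up by the lockdown and that "we will measure the ST and physical activity again before delivering the intervention"; delivery began in November 2020. The Postintervention Assessment section places t0 only before the intervention, which fits either measurement.

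On allocation, the Randomization section says that "restricted randomization will be done so that intervention and control groups have a similar number of families from high, middle, and low socioeconomic groups", and that "Geographical differences (urban and slum areas) in the study area will also be considered during randomization to avoid contamination".

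The Data Management and Analysis section lists summaries, correlations, chi-square tests, relative risks and relative risk reduction, under intention-to-treat and per-protocol analyses. It gives no test or model for continuous screen time, and mentions neither baseline screen time nor the restriction factors as covariates.

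**The concern.** A change score does not have the same variance as a single measurement. If the SD is the same at both times, its variance is 2(1 − rho) times that of screen time: larger when rho is below 0.5, smaller when it is above. The sample size therefore fits the stated outcome at one value of rho only, and the article does not give rho.

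The unnamed baseline matters for the same reason. One candidate was taken before the lockdown and the other shortly before delivery. They define different changes and may correlate differently with follow-up.

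Enrolment is complete at 440, so the choice of analysis is the main remaining influence on precision. Regressing follow-up on baseline is never less precise than the change score in large samples, and it makes use of the factors that the randomisation was built to balance.

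**Working it through.** **Inputs.** From Sample Size: SDs 2.09 and 1.46, difference 0.54, z = 1.96, power 80%, 10% attrition. From Results: 440 enrolled. Assumptions: 1:1 allocation; rho, shown as a range; within each arm, the same SD at baseline and follow-up.

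**The plan's own figure.** V = 2.09² + 1.46² = 4.3681 + 2.1316 = 6.4997. Then n = V(1.96 + 0.84)²/0.54² = 6.4997 × 7.84/0.2916 = 174.75, or 175 per arm. The stated 170 is within 3% of this and has power 78.9% for a comparison of follow-up means. The small difference is not the point here.

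**Evaluable number.** 440/2 = 220 per arm; 220 × 0.90 = 198.

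**Power.** Φ(0.54/√(V·m/n) − 1.96), where m = 2(1 − rho) for the change score and m = 1 − rho² for ANCOVA.

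Worked case, rho = 0.3, n = 198:
- Change: m = 1.4; √(6.4997 × 1.4/198) = 0.2144; 0.54/0.2144 − 1.96 = 0.56; power 71.2%.
- ANCOVA: m = 0.91; √(6.4997 × 0.91/198) = 0.1728; 0.54/0.1728 − 1.96 = 1.16; power 87.8%.

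| rho | m, change | m, ANCOVA | Change, n = 198 | ANCOVA, n = 198 | Change, n = 170 | ANCOVA, n = 170 |
|---|---|---|---|---|---|---|
| 0.2 | 1.60 | 0.96 | 65.4% | 86.0% | 58.8% | 80.5% |
| 0.3 | 1.40 | 0.91 | 71.2% | 87.8% | 64.6% | 82.5% |
| 0.4 | 1.20 | 0.84 | 77.7% | 90.2% | 71.3% | 85.4% |
| 0.5 | 1.00 | 0.75 | 84.6% | 93.1% | 78.9% | 89.0% |
| 0.6 | 0.80 | 0.64 | 91.5% | 96.1% | 87.0% | 93.2% |
| 0.7 | 0.60 | 0.51 | 97.0% | 98.7% | 94.6% | 97.2% |

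**Where change-score power crosses 80%.** About rho = 0.43 at 198 per arm and 0.51 at 170.

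**Number needed per arm for 80% power.** At rho 0.3, 245 for change and 160 for ANCOVA; at 0.5, 175 and 132; at 0.7, 105 and 90.

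**Why the ranking does not depend on rho.** 1 − rho² = (1 − rho)(1 + rho), and 1 + rho ≤ 2, so the ANCOVA multiplier never exceeds 2(1 − rho). It never exceeds 1 either, so ANCOVA is also at least as precise as comparing follow-up means alone.

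**Sensitivity.** Randomised arms should share one baseline SD. With 2.09 at baseline in both arms and 198 per arm, change-score power drops to 63.8% at rho 0.3 and 77.6% at rho 0.5, while ANCOVA is almost unchanged (87.7% and 92.8%). The crossing point of 0.43 is thus tied to the equal-SD assumption.

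**The case against.** The strongest reply is that the article never states an unadjusted comparison. A reader might infer from the word change that raw change will be tested without covariates. The documents do not support that: the Outcomes section defines an outcome, not a model, and the analysis section names none for continuous screen time. An outcome defined as change is also compatible with adjustment, because regressing change on arm and baseline gives the same arm effect as regressing follow-up on arm and baseline. Covariates are often left to an analysis plan, which is not shown here. This stands, and silence about the model is not counted as a fault.

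A reader might also infer that the trial is underpowered because reports on either side of a lockdown must correlate weakly. That is not supported either. The article gives no correlation, and from rho 0.5 upward at 198 per arm the change score exceeds 80% on the planning SDs. If the re-measurement is t0, the lockdown interval that delayed the start does not separate it from the assessment after 8 weeks of intervention.

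On the restriction factors, leaving them out is conservative rather than invalid, and the article does not show how prognostic they are. The gain from including them cannot be quantified.

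One limit applies to any use of baseline. The Randomization section places data collection after allocation and in the hands of the person who allocates, so knowledge of arm could colour the baseline report. A change score carries such an error at full weight; ANCOVA carries it only in proportion to the baseline slope.

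What remains is what the article itself states: a change outcome sized on group SDs, and two candidate baselines with neither named.

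**Conclusion.** The point holds as a mismatch to clarify and an improvement that costs nothing, not as a proven loss of power. Outcome and sample size agree only at rho = 0.5, and the value to be subtracted is undefined. If change is compared directly, ANCOVA on the same 198 per arm would add about 21 percentage points of power at rho 0.2, 17 at 0.3, 12 at 0.4, 9 at 0.5 and 5 at 0.6. These figures rest on the planning SDs, equal SDs over time, 1:1 allocation, 10% loss and an assumed rho. If 2.09 and 1.46 were in fact SDs of change, the shortfall would not arise, but the Sample Size section labels them as group SDs.

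Three neighbouring matters are separate and not settled here: whether weighted average or weekday and weekend screen time is primary, which assessment time is primary, and whether considering area in the randomisation can prevent contamination.

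**What to change.** 1. State that t0 for screen time is the re-measurement taken immediately before the intervention, and that it covers both arms.
2. For each primary screen-time measure that the protocol already defines, estimate the arm effect by ANCOVA: follow-up screen time on arm, the t0 value, socioeconomic group and urban/slum area. Use robust standard errors, because the planning SDs differ between arms.
3. In the Sample Size section, say that 2.09 and 1.46 are SDs of screen time at one time point (if that is what they are), and state the rho under which they apply to the chosen analysis.

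The cost is wording. The covariates are collected or already planned, and no further participants are needed. The change should be recorded before outcome data are examined by arm.

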We used the 5 progressive physical activity levels among preschoolers given in the Preschool Physical Activity Questionnaire (PrePAQ) to assess physical activity. The PrePAQ categorizes activity into stationery (no action), sedentary (limb or trunk movement), slow-paced (moving easily or slowly), medium-paced (moving at a moderate pace), and fast-paced (quick pace or hard effort) [43].

The standard Preschool Child Behavior Check List was used to assess the child’s emotional and behavioral development. It has been validated in an Indian setting and has the right internal consistency (Cronbach α=0.95) [44]. It consists of 100 items with a 3-step response scale (0, 1, and 2). These items are scored as being absent (score, 0), occasionally present (score, 1), and very often present (score, 2).

The sleep disturbances scale for children was used to measure the child’s sleep patterns. It is a 26-item Likert-type scale that measures specific sleep disorders along with overall sleep disturbances in children. It has been validated and has an internal consistency of 0.71-0.79, test-retest reliability of 0.71, and diagnostic accuracy of 0.91 [40].

The lead author visited the homes of the study families and conducted face-to-face interviews during the baseline assessment.

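### For the behaviour and sleep scales, the only named between-arm methods apply to a proportion; the baseline-adjusted score should be the analysed outcome, with the proportion as support

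*Protocol article*

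**What the plan says.** Under Outcomes, the secondary outcomes include the "proportion of children with emotional behavior problems, and sleep disturbances". The next sentence adds: "For emotional behavior and sleep disturbances, the change in scores as per the tools will be noted". On the natural reading, the word proportion governs both conditions, although the comma leaves its reach over sleep open. The article does not say which form is the outcome and which is supportive, and its text gives no cut-off for either tool.

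Both tools give numeric scores. Of the behaviour checklist, Baseline Assessment says: "It consists of 100 items with a 3-step response scale (0, 1, and 2". The sleep scale is described there as a 26-item Likert-type instrument.

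Under Data Management and Analysis, the rule for categorical variables is: "Categorical variables will be summarized as proportions, and differences between groups will be tested using chi square tests". For continuous variables it is: "Continuous variables will be summarized as means with interquartile ranges and standard deviations", with correlations also to be estimated. The effect measure is a risk measure: "The effectiveness of the intervention will be estimated by calculating the relative risk reduction (1-relative risk"). A P value below .05 counts as significant in every analysis.

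**The concern.** Each scale has two candidate outcomes, and the methods that the article names fit only one of them. A statistician who followed the text would classify each child as a case or non-case, run a chi-square test and report a relative risk reduction. The scores would be described but not compared between arms.

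Two things are at stake. First, cutting a graded score at a threshold ignores improvement that does not carry a child across it, so a real shift can be reported as no effect. Second, with two unranked forms and one significance threshold for all analyses, either form can be given prominence once the results are known. This matters more here because the outcomes are caregiver-reported and the trial is unblinded.

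For its other outcomes the article prefers means. The Discussion says that screen time was planned as a mean and not a proportion, and physical activity is a mean change in minutes. No reason is given for treating these two scales differently.

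**Working it through.** **The plan's own figures.** There is no sample size, power, prevalence or cut-off for the behaviour or sleep outcomes. The Sample Size section concerns screen time only. Its formula gives (2.09² + 1.46²)(1.96 + 0.84)²/0.54² ≈ 174.8, or 175 per arm, against the stated 170. That difference is small and has no bearing here.

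**Inputs from the article.** 440 enrolled in total (Results); 10% attrition (Sample Size); significance at .05, taken as two-sided.

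**Assumptions.**
- Scores are roughly normal with equal spread in both arms.
- Allocation is equal, so 440/2 = 220 and 220 × 0.90 = 198 per arm are analysed.
- The effect is 0.3 SD. The article gives none for these scales. As a point of reference only, the screen-time assumption is of that size: 0.54/√[(2.09² + 1.46²)/2] = 0.54/1.803 ≈ 0.30.
- The control prevalence p of cases is unknown and is varied from 10% to 50%.

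**Step 1: information kept.** The efficiency of the proportion relative to a comparison of mean scores is φ(z)²/[p(1 − p)], where z is the normal cut-off with upper tail p and φ is the normal density.

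| p | φ(z) | efficiency | information lost |
|---|---|---|---|
| 50% | 0.399 | 0.64 | 36% |
| 30% | 0.348 | 0.58 | 42% |
| 20% | 0.280 | 0.49 | 51% |
| 10% | 0.175 | 0.34 | 66% |

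The loss reaches one half at p of about 21%. A median split is the most favourable case.

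**Step 2: power on the score.** Φ(0.3 × √(198/2) − 1.96) = Φ(2.985 − 1.96) ≈ 85%.

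**Step 3: power on the proportion.** The same 0.3 SD shift lowers prevalence to p₂ = Φ(−(z + 0.3)). Power is Φ((p − p₂)/SE − 1.96), with SE = √{[p(1 − p) + p₂(1 − p₂)]/198}.

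| p | p₂ | (p − p₂)/SE | power |
|---|---|---|---|
| 50% | 38.2% | 2.38 | 66% |
| 30% | 20.5% | 2.19 | 59% |
| 20% | 12.7% | 1.98 | 51% |
| 10% | 5.7% | 1.60 | 36% |

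Using the pooled null variance lowers these by about half a percentage point at most.

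**Step 4: check at the planned size.** With 170 per arm, a comparison of means has 80% power for a shift of 0.304 SD. For that shift the proportion gives 60%, 53%, 46% and 32% power at the same four prevalences. Restoring 80% would take 271, 319, 390 and 596 per arm.

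**Step 5: effect of baseline adjustment.** Steps 1 to 4 compare unadjusted follow-up scores. With baseline correlation r, adjustment multiplies the variance by 1 − r², which never exceeds 1. A simple change score multiplies it by 2(1 − r), which exceeds 1 when r is below 0.5. At an assumed r of 0.5 the adjusted factor is 0.75, and the proportion's efficiency at a median split falls from 0.64 to 0.64 × 0.75 = 0.48. The article gives no value of r.

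**The case against.** The strongest reply is that the score has not been set aside. Change in score stands under Outcomes, and the sentence can be read as saying how the two outcomes will be measured. The chi-square sentence is a general rule for categorical variables that names neither scale. No between-arm test is named for any continuous variable, including the primary screen-time outcome, so the silence on scores may only reflect a condensed article whose analysis plan is not shown. Reporting a clinically readable proportion beside a score is also ordinary practice for secondary outcomes.

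Much of this stands. A reader might infer that the plan throws the scores away, or that it expressly orders a chi-square test for these two outcomes. It says neither: the scores are collected and kept, and the link to chi-square is an inference from calling the outcome a proportion. The absence of a named score test would not be a point by itself.

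What remains is what the article does state. It defines the outcome as a proportion, places a second form beside it without rank, and names effect measures that fit only the first. Which form is the outcome is a matter of outcome definition, not of analysis detail.

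**Conclusion.** The point holds as a cheap improvement to two secondary outcomes. As written, the tested form is the proportion, and it carries less information than the score at every prevalence examined under the working's assumptions.

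The size is conditional. A reader might conclude that half or more of the information is lost. That is true only if about 21% or fewer of the children are cases. The Abstract describes the children as healthy and Study Population excludes diagnosed chronic illness, which makes a low prevalence plausible but does not establish it. What can be said is a loss of about 36% at best, rising to 66% at 10% prevalence. These figures rest on a roughly normal score compared at follow-up without adjustment. The power figures also depend on the assumed 0.3 SD effect and 198 per arm.

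The primary outcome and the stated sample size are untouched.

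**What to change.** For each scale, state that the analysed secondary outcome is the between-arm difference in total score, adjusted for the baseline score. Report the proportion above the tool's cut-off, with the cut-off named and a confidence interval given, as supportive description. Record this before the arms are compared.

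The cost is wording only, since both tools are already administered at baseline and follow-up. There are two small downsides. The headline result will be in score points, which are less immediate to readers than a share of children; the supportive proportion meets that need. The gain from adjustment may also be modest: the Results section plans to remeasure only screen time and physical activity before delivery, so the behaviour and sleep baselines date from December 2019 to March 2020, while the intervention began in November 2020. An old baseline weakens the correlation and hence the gain in precision. It also favours adjustment over a simple change score, which loses precision relative to the follow-up score alone when that correlation is below 0.5.
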